#### Power and Sample Size Calculation

Forty-three emerging adults will be recruited for this study in the vocational integration program. The number of participants needed is based on an *a priori* power analysis using G*Power software (*F*-test, ANOVA: repeated measures, within factors; 1−β = 0.95, *α* = 0.05, Cohen’s *f* = 0.25), which revealed that the study would require a total sample size of *N* = 43 (Faul et al., 2007). An additional nine participants have been added to this estimated sample size to account for an assumed 20% dropout rate, which increases the required total sample size of *N* = 52. The dropout rate has been chosen according to current standards.

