## Abstract

**Background:** Emerging adults who do not successfully transition from compulsory education to the upper secondary level have a greater risk of developing mental illness than their working peers. Early intervention is important in these cases; the course of an illness can be positively influenced if treated early and without delay, and consequently, the illness will not affect the professional and personal development of the emerging adults any further. Postponing treatment of a mental illness increases the risk of chronification of the disease. Up to now, vocational integration programs have been mostly educationally oriented. To recognize and treat mental illness in a timely way, we developed an intervention that includes psychotherapy support in a vocational integration program for emerging adults who have not successfully transitioned from compulsory education to the upper secondary level.

**Aim:** The aim of this study is to investigate the effectiveness of the described intervention, which will be delivered to all emerging adults aged 16–29 entering the vocational integration program. Another objective is to determine if it is worthwhile and feasible to proceed with testing the intervention in a full-scale clinical trial. Conducting research with this population can be very difficult, which makes it especially important to test the feasibility of a clinical trial.

**Methods:** A single group clinical trial will be conducted to examine the effectiveness of the intervention described above. Emerging adults aged 16–29 entering a vocational integration program will be recruited. Participants will provide informed consent and complete pre-intervention measures; they then take part in the intervention group in addition to the regular vocational integration program. The primary outcomes for this study are an increase in work ability, mental health literacy, and mental health. Demographic information, vocational biography, and satisfaction with the intervention will also be collected. Questionnaire data will be collected at pre-intervention, post-intervention, and 6-month follow-up.

**Ethics and dissemination:** The study was approved by the Ethics Committee of the Canton of Zurich (2017-00936) and registered in https://clinicaltrials.gov (NCT03328286) before recruitment started. The results will be reported in future scientific publications and international conference presentations.

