## Materials and Methods

### Study Design

This is a single-center naturalistic study involving a repeated measure design with three assessments (pre-intervention, post-intervention, and 6-month follow-up). Six month is a common time period for follow up assessments. It allows to collect meaningful data and the risk for ‘lost to follow up’ is reduced compared to longer time periods.

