#### Analysis

Besides descriptive data analysis, we will analyze changes in the main outcome measures from pre- to post-intervention and at 6-month follow-up. To analyze the data, we will employ a linear mixed model (LMM). This type of model is particularly useful in settings where repeated measurements are made with the same participants (longitudinal study). Linear mixed models also incorporate both fixed and random effects. Since we are expecting a dropout rate of 20%, a particular advantage of linear mixed models is how they deal with missing values, and we therefore prefer it over more traditional approaches such as repeated measures ANOVA. Participants with partial data sets can be included in the analysis. When testing the hypotheses, the level of significance used will be 5% (*α* = 0.05). Alpha adjustment will be used. The statistical analysis of the data will be done using the software package IBM SPSS Statistics Version 24.

To determine the feasibility of conducting a full clinical trial and implementation of the intervention, we will describe the following aspects of the data: adherence to the group meetings, recruitment feasibility, acceptance of this intervention among professionals and the emerging adults in the vocational integration program. These data will be gathered partially through the psychotherapist (adherence to group meeting) but mostly through interviews at the end of the study. The final report will summarize the data to support a clear decision on whether and how to proceed with a full trial and to inform development of the study procedures to maximize the quality of the trial design.

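### The sample size paragraph gives 43 and 52 as competing recruitment numbers; as a minor point, the allowance behind 52 covers about 17% dropout, not 20%

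*Protocol article*

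**What the plan says.** All the sample size figures stand in one paragraph of the protocol article, under Power and Sample Size Calculation.

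- Opening sentence: "Forty-three emerging adults will be recruited for this study in the vocational integration program".
- Basis: a G*Power calculation with "ANOVA: repeated measures, within factors; 1−β = 0.95, *α* = 0.05, Cohen’s *f* = 0.25". Its result is given as 43.
- Dropout allowance: "An additional nine participants have been added to this estimated sample size to account for an assumed 20% dropout rate". The paragraph closes by putting the total needed at 52.

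The Study Design section sets three assessments, and the Abstract describes a single group. The Analysis section repeats the 20% dropout expectation and gives it as a reason to prefer a linear mixed model over repeated measures ANOVA, because participants with incomplete data can then be kept. The Discussion repeats the 20% once more. No section outside the sample size paragraph says how many people are to be enrolled.

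**The concern.** The one sentence that says how many people will be recruited uses the figure that the next sentence presents as the requirement before dropout. If 43 are recruited and 20% are lost, 43 cannot remain. If 52 are recruited, the opening sentence is wrong.

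This matters beyond tidiness because the Objectives include judging the feasibility of recruitment and uptake. A study that enrolled 45 would have exceeded one stated target and missed the other.

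A second, smaller problem is how 52 was reached. Nine is 20% of 43, rounded up. Dropout acts on the number recruited, not on the number of completers wanted, so the allowance falls slightly short of the rate it is meant to cover.

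**Working it through.** **Inputs from the article.** One group; m = 3 assessments; f = 0.25; α = 0.05; target power 0.95; required N = 43; nine added; total 52; dropout 20%.

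**Assumptions.** The article does not give the correlation among repeated measures (ρ) or the nonsphericity factor (ε). I take ρ = 0.5 and ε = 1.

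**1. Reproducing 43.** For the within-factor repeated measures F-test, the noncentrality is λ = f² · n · m · ε / (1 − ρ), with degrees of freedom (m − 1)ε and (n − 1)(m − 1)ε.

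- n = 43: λ = 0.0625 × 43 × 3 / 0.5 = 16.125, df 2 and 84, power 0.951.
- n = 42: λ = 15.75, df 2 and 82, power 0.947.

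So 43 is the smallest n that reaches 0.95, and the stated figure reproduces exactly. It depends heavily on ρ: with ε = 1 the required N is 84 at ρ = 0, 60 at 0.3, 43 at 0.5 and 27 at 0.7. The values 0.5 and 1 are used because they return the plan's own number, not because the plan states them.

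**2. Reproducing 52.** 43 × 0.20 = 8.6, rounded up to 9, and 43 + 9 = 52. Equivalently, 43 × 1.20 = 51.6, so 52.

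**3. Inflation that retains 43.** 43 / (1 − 0.20) = 53.75, so 54. The loss that 52 can absorb while leaving 43 is 9/52 = 17.3%.

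**4. Expected completers and complete-case omnibus power at 20% loss.**

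| Recruited | Expected completers | Power (ρ = 0.5, ε = 1) |
|---|---|---|
| 43 | 43 × 0.80 = 34.4 | 0.888 at 34 |
| 52 | 52 × 0.80 = 41.6 | 0.941 at 41; 0.947 at 42 |
| 54 | 54 × 0.80 = 43.2 | 0.951 at 43 |

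The completer counts need no assumption about ρ or ε; the power figures do.

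**The case against.** The best defence is that the paragraph largely resolves itself. It labels 43 as the output of the power analysis, says that participants were added to it, and finishes with 52 as the required total. Read as a whole, 52 is the natural target and the opening sentence simply carries the wrong number. That stands, and it makes the outcome with 34 completers the less likely reading. It does not remove the need to correct the sentence, since nothing else in the article confirms 52.

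The second defence is that completer-based power is not power for the planned analysis. The mixed model keeps participants with partial data, so complete-case figures probably overstate the loss. This also stands, with limits. The main hypothesis concerns change from baseline to the 6-month follow-up, and for that contrast a participant missing the last assessment adds back only part of the information. The plan also sized the study on repeated measures ANOVA and added people for dropout, so it treated dropouts as needing replacement.

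Third, the inflation slip is small: two participants, and less than one percentage point below 95%. That is correct, and it is why this is a side note.

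A reader might infer more: that enrolment will halt at 43, so the study will run at about 89% power. The article does not support that. It contains no rule that ends recruitment at either number; it gives only an 18-month study duration and warns that recruiting the required sample may be difficult.

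**Conclusion.** The contradiction is real and lies in the current text: 43 is given both as the number to recruit and as the requirement before dropout, while 52 is given as the required total. The gap is nine participants.

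The allowance behind 52 is a minor error. It falls two short of 54 and covers about 17% loss. On the likely reading (52 recruited), complete-case omnibus power at 20% loss is about 94 to 95%. On the literal reading of the opening sentence it is about 89%. Both power figures rest on ρ = 0.5 and ε = 1 and refer to the omnibus repeated measures ANOVA used for sizing, not to the mixed-model test of the main hypothesis.

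It would go too far to conclude that the trial is materially underpowered by this slip, or that its results would be invalid. The point should be corrected, but it ranks below the changes that the study could not proceed without.

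**What to change.** Rewrite the opening sentence so that it states a single recruitment target, and describe 43 as the number needed with complete data. Then choose one of two options:

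- **Keep 52.** Say that it covers about 17% loss, and that at 20% loss about 41 to 42 completers are expected, with about 94 to 95% complete-case power for the omnibus repeated measures ANOVA. State the correlation and epsilon used, and make clear that this is not the power of the planned mixed-model test.
- **State 54.** Show 43/(1 − 0.20) = 53.75, rounded up, if 95% on the sizing basis is to stand. State the correlation and epsilon here too.

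The cost is one or two sentences, plus two further participants under the second option. The design and the analysis do not change.

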#### Analysis

Besides descriptive data analysis, we will analyze changes in the main outcome measures from pre- to post-intervention and at 6-month follow-up. To analyze the data, we will employ a linear mixed model (LMM). This type of model is particularly useful in settings where repeated measurements are made with the same participants (longitudinal study). Linear mixed models also incorporate both fixed and random effects. Since we are expecting a dropout rate of 20%, a particular advantage of linear mixed models is how they deal with missing values, and we therefore prefer it over more traditional approaches such as repeated measures ANOVA. Participants with partial data sets can be included in the analysis. When testing the hypotheses, the level of significance used will be 5% (*α* = 0.05). Alpha adjustment will be used. The statistical analysis of the data will be done using the software package IBM SPSS Statistics Version 24.

To determine the feasibility of conducting a full clinical trial and implementation of the intervention, we will describe the following aspects of the data: adherence to the group meetings, recruitment feasibility, acceptance of this intervention among professionals and the emerging adults in the vocational integration program. These data will be gathered partially through the psychotherapist (adherence to group meeting) but mostly through interviews at the end of the study. The final report will summarize the data to support a clear decision on whether and how to proceed with a full trial and to inform development of the study procedures to maximize the quality of the trial design.

## Discussion

On-site psychotherapy support in a vocational integration program, as we have planned for in this study, has the potential to address many of the practical barriers to help-seeking behavior in emerging adults. The strengths of the proposed research are threefold: first, we address a research gap by focusing on emerging adults in a vocational integration program. As opposed to students or unemployed emerging adults, this population has not been well studied. Second, several studies have examined rates of use of mental health services by adolescents and emerging adults. However, most have been U.S.-based studies (Kessler et al., 2001). The studies show that the rate of use of services is low among adolescents and emerging adults aged 15–24 and that up to 80% of children and adolescents aged 6–17 do not receive needed mental health services (Kataoka et al., 2002). In Switzerland, the rates of use of mental health services are lower, with 5% of 15- to 25-year-olds reporting using mental health services (Bundesamt für Statistik, 2014). The intervention that we propose in this study is innovative for vocational integration programs. Through the implementation of this low-threshold intervention, we hope to increase the rate of use of mental health services by emerging adults, but we also aim at improving early recognition of mental health disorders and appropriate therapy for emerging adults. Third, the intervention contributes to better integration of emerging adults with mental health disorders in the labor market and thus in society.

Despite these strengths, the use of a single group repeated measure design is a methodological weakness that results in the inability to control for potential confounders. In order to have something similar to a control group, we will compare historical data from previous participants of the vocational integration program with data from the current participants. We will use the data from participants who have attended the program for up to 2 years from the start of our study and do a matching with the current sample. We will not be able to compare many indicators, but we can compare the follow-up solution after leaving the vocational integration program, the length of stay in the program, etc., with the current sample. When making this type of comparison, it must be considered that important external factors such as the current labor market situation can have an impact on the abovementioned indicators.

However, we also face possible problems when recruiting the required sample. Emerging adults with mental health disorders in vocational integration programs are already under a lot of societal pressure. We therefore reckon with a 20% dropout rate. Additionally, they stay in the program from 4 months up to a year; this gives us a limited statistical population. Under these conditions, it would not be feasible to implement the study as a part of a randomized controlled trial. Therefore, the present study aims to test a number of important feasibility questions and to try to overcome the barriers that have been identified. Although this limitation might temper the conclusions regarding the effectiveness of the intervention, the strengths of this study have the potential to bring significant knowledge to research and to public policy.

## Ethics and Dissemination

The study has been approved by the Ethics Committee of the Canton of Zurich (Switzerland). After study completion, the results will be published in international peer-reviewed journals. If they provide valid and reliable information in addition to traditional measures, the findings will be presented at international symposiums with the aim to consider ways to develop new research protocols on emerging adults with mental health disorders in vocational programs.

Plans concerning data sharing do not exist at this time.

## Declarations

### Ethics Approval and Consent to Participate

The Ethics Committee of the Canton of Zurich provided ethics approval for the study (2017-00936). Participants will read an information statement and give informed consent before participating in the study. For participants who have not yet reached legal age, the data protection officer states that young people aged around 14 are assumed to be capable of making judgments with regard to questions that exclusively concern their interests. Therefore, no informed consent from a legal guardian is needed. Any modifications of the trial protocol will be communicated to the Ethics Committee and ClinicalTrials.gov.

## Ethics Statement

This study will be carried out in accordance with the recommendations of Federal Act on Research involving Human Beings, Swiss Ethics Committees on research involving humans. The protocol was approved by the Ethics Committee of the Canton of Zurich. All subjects will give written informed consent in accordance with the Declaration of Helsinki.

## Abbreviations

BSI: Brief Symptom Inventory
CES-D: Center for Epidemiological Studies Depression Scale
GHSQ: General Help-Seeking Questionnaire
GLM: Generalized linear model
M-CIDI: Munich-Composite International Diagnostic Interview
MHLS: Mental Health Literacy Scale
PSQ: Perceived Stress Questionnaire
RSES: Rosenberg Self-Esteem Scale
SWE: Allgemeine Selbstwirksamkeitserwartung
VET: Vocational education and training
WAI: Work Ability Index.
